		***Measurement timepoints (T0 – Tz) and days post-Tx***										
**Variables**	**Measurements**	**T0a**	**T0b**	**T1**	**T2**	**T3**	**T4**	**T5**	**T6**	**T7**	**T8**	***Tz***
		**−10**	**30**	**60**	**90**	**120**	**150**	**180**	**240**	**300**	**365**	***455***
**Primary outcome**												
Re-hospitalisation rate (number of re-hospitalisations per patient year)	FIMA**©** (10 Items) [83] Medical Records, CRF											
**Secondary outcomes**												
Healthcare utilisation costs	FIMA**©** (10 Items) [83]			**X**	**X**	**X**	**X**	**X**	**X**	**X**	**X**	**X**
	Swiss standardised unit costs [84, 85]			**X**	**X**	**X**	**X**	**X**	**X**	**X**	**X**	**X**
Length re-hospitalizations	FIMA**©** (10 Items) [83] Medical Records, CRF			**X**	**X**	**X**	**X**	**X**	**X**	**X**	**X**	**X**
Medication adherence (implementation & persistence dimension [67])	Electronic Monitoring: MEMS® Button [86]											
	BAASIS**©** (implementation 4 items; persistence: 1 item) [87]		**X**	**X**	**X**	**X**	**X**	**X**	**X**	**X**	**X**	**X**
Treatment burden	PETS**©** (60 items) [88]	**X**			**X**			**X**			**X**	
Health-related Quality of Life	EQ-5D-5L**©** (5 items) [89]	**X**	**X**	**X**	**X**	**X**	**X**	**X**	**X**	**X**	**X**	**X**
Quality-Adjusted Life Year (QALY)	EQ-5D-5L**©** (5 items) [89], value set for Germany EQ-VT v. 2.0 (116)	**X**	**X**	**X**	**X**	**X**	**X**	**X**	**X**	**X**	**X**	**X**
Incidence/grade chronic and acute GvHD	Medical record, CRF		**X**	**X**	**X**	**X**	**X**	**X**	**X**	**X**	**X**	
Overall survival rate	Medical record, CRF		**X**	**X**	**X**	**X**	**X**	**X**	**X**	**X**	**X**	**X**
Conditioning regimen	Medical record, CRF	**X**										
Donor match/type	Medical record, CRF	**X**										
Disease	Medical record, CRF	**X**										
Disease status at transplant	Medical record, CRF	**X**										
If death: Date and cause of death	Medical record, CRF		**X**	**X**	**X**	**X**	**X**	**X**	**X**	**X**	**X**	**X**
If relapse: Date of relapse	Medical record, CRF		**X**	**X**	**X**	**X**	**X**	**X**	**X**	**X**	**X**	**X**
**Demographics**												
Age	Medical Record, CRF	**X**										
Sex	Medical Record, CRF	**X**										
Education	Questionnaire (4 items)	**X**										
Living alone	Questionnaire (1 item)	**X**										
**IMPLEMENTATION OUTCOME DATA (from intervention group / care coordinator team)**												
Acceptability	AIM (4 items) [90]	**X**	**X**	**X**	**X**	**X**	**X**	**X**	**X**	**X**	**X**	
Appropriateness	IAM (4 Items) [90]	**X**	**X**	**X**	**X**	**X**	**X**	**X**	**X**	**X**	**X**	
Feasibility	FIM (4 items) [90]	**X**	**X**	**X**	**X**	**X**	**X**	**X**	**X**	**X**	**X**	
Technology feasibility	N (days with data entry), N (technical problems)											
Intervention fidelity	N (visits), Minutes (visits), N (Behavioural Change Techniques) compared to protocol											
Intervention fidelity	5% of intervention sessions will be randomly selected to be audiotaped and checked for protocol congruence											

*Abbreviations. AIM* Acceptability of Intervention Measure, *BAASIS* Basel Assessment of Adherence to Immunosuppressive Medication Scale, *CRF* case report form, *FIM* Feasibility of Intervention Measure. *IAM* Intervention Appropriateness Measure, *MEMS* Medication Event Monitoring System, *PETS* Patient Experiences with Therapy and Self-management, *Tx* transplantation

#### Variables and measurement

Effectiveness outcomes (Table 3) will be assessed in the IG and UCG at the time of inpatient stay and during regularly scheduled outpatient appointments. After completion of the intervention period, a three-month follow-up is planned to assess sustained health outcomes by further assessing effectiveness outcomes in both groups (see also below).

**Table 3 Tab3:** Effectiveness outcomes

Outcome variable(s)	Measure(s) and data collection procedures	Data source and reporter (when applicable)
**Primary Outcome**		
Re-hospitalisation rate	Number of events after the initial post-alloSCT discharge per patient in the first year post-alloSCT	EHR
**Secondary Outcomes**		
Healthcare utilization costs	(1) Calculated from the payers’ perspective based on standardised unit costs of resources in Switzerland [84, 85, 91]	EHR
	(2) Medical records and an adapted version of the generic FIMA© self-reporting questionnaire for elderly persons [83]: 7 items, asking retrospectively for number of visits to physicians, days/hours of ambulatory healthcare visits, days/hours of home care services received, days/hours of support by family caregivers, type(s) and duration(s) of rehabilitation therapy, reason(s) and duration(s) of inpatient days (including intensive care unit stays and/or emergency room visits), and current type of insurance.	Paper survey (pat.)
Length re-hospitalizations	(1) The total length of inpatient re-hospitalizations in the first year after alloSCT is the total number of hospitalized days (planned and unplanned) after initial post-alloSCT discharge until end of study, like reported in all medical reports and the generic FIMA© self-reporting questionnaire for elderly persons [83]	Paper survey (pat.) and EHR
Medication adherence (implementation & persistence dimension [67])	(2) Implementation & persistence dimension [67] will be assessed using the Basel Assessment of Adherence to Immunosuppressive Medication Scale (BAASIS©): a validated self-report measure assessing adherence to implementation issues (e.g., drug holidays; 4 items; yes/no) and persistence/discontinuation (1 item; yes/no) [87].	Paper survey (pat.)
	(3) Daily intake (date and time) of immunosuppressive medication will be monitored electronically via the MEMS® Button, [86] which has been indicated previously as the preferred electronic monitoring device [63]. Patients will receive the button shortly before discharge and are instructed on how to use it at home until their immunosuppressants are discontinued. Data will be password-protected and stored on the MEMS® Adherence Software database, which provides an overview of the electronically compiled dosing history per patient [86].	MEMS® Button [86]
Treatment burden	German version of the PETS© self-reporting questionnaire [88]: nine multi-item domain scales, each measuring the burden of one aspect of chronic illness treatment on a 4- or 5-point Likert-type response scales regarding a 4-week recall time frame: medical information (7 items); medications (7 items); medical appointments (3 items); health monitoring (2 items); interpersonal challenges (4 items); health care expenses (5 items); difficulty with health care services (7 items); role/social activity limitations due to self-management (6 items); and physical/mental exhaustion due to self-management (5 items). Raw domain scores are transformed to a standardised 0-to-100 metric, with higher scores indicating greater treatment burden.	Paper survey (pat.)
Health-related Quality of Life	Measured using the EQ-5D-5L© [89], covering five dimensions (mobility, self-care, usual activities, pain/discomfort and anxiety/depression) and including the EQ–Visual Analogue Scale (VAS), on which individuals rate their overall perceived health state (scale of 0 to 100)	Paper survey (pat.)
Quality-Adjusted Life Year (QALY)	Calculate QALY: Generating these requires the HRQL preference weight (obtained from the EQ-5D-5L© value set for Germany EQ-VT v. 2.0) [92] and time in days between HRQL measurements [93]. QALY scores range from 1 (perfect health) to 0 (dead) [94].	Paper survey (pat.)
GvHD	Incidence and grade of chronic and acute GvHD	EHR
Overall survival rate	Overall survival rate from start of study participation	EHR
Conditioning regimen	Treatments used to prepare a patient for stem cell transplantation (e.g., chemotherapy, monoclonal antibody therapy, and radiation to the entire body)	EHR
Donor match/type	Human leukocyte antigen (HLA) tissue type	EHR
Disease	Primary disease	EHR
If death	Date and cause of death	EHR
If relapse	Date of relapse	EHR

*Abbreviations. BAASIS* Basel Assessment of Adherence to immunosuppressive medication scale. *EHR* Electronic Health Record, *EQ-5D-5L*© European Quality of Life 5 Dimensions 5 Level Version, *EQ-VT* EQ valuation protocol, *GvHD* Graft-versus-Host-Disease, *HRQL* health related quality of life, *pat* patient, *PETS* Patient Experiences with Therapy and Self-management, *QALY* quality-adjusted life years

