### The SMILe project: a two-phase implementation science project

Our project—the development/adaption, implementation and evaluation of an ICM in allogeneic stem cell transplantation facilitated by eHealth (SMIL*e-ICM*)—was designed to anticipate and address these methodological challenges to sustainably reengineer the follow-up care of alloSCT patients in a Swiss and German setting. AlloSCT patients are a growing group with complex care needs. In 2019, 43′581 patients across 51 countries received allogeneic stem cell transplants [42]. Despite improved long-term survival, mortality and re-hospitalisation rates remain substantial, especially in the first year post-alloSCT [43]. In particular, the first months post-alloSCT constitute the most complex phase in terms of life-threatening complications such as infections, acute graft-versus-host disease (aGvHD) and gastrointestinal complications [44–49]. Avoiding re-hospitalisations or at least shortening re-hospitalisation stays will require early detection and treatment of complications [50, 51]. To achieve that goal, alloSCT patients will need to self-manage complex therapeutic regimens; however, non-adherence is common [52–54]. While eHealth has been applied to deliver individual self-management support interventions [55, 56] or caregiver support [57] in alloSCT, the SMILe-ICM is novel. As a full-scale care model, it has the potential, when successfully implemented, to optimise care processes and ultimately improve this vulnerable group’s health outcomes.

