**Aim 1** has two parts**:**

**1a.** to evaluate the SMILe-ICM’s effectiveness in view of one primary outcome—re-hospitalisation rate—and seven secondary outcomes—total healthcare utilization costs, total length of inpatient re-hospitalizations, medication non-adherence, treatment burden, health-related quality of life (HRQL), quality-adjusted life year (QALY), acute and chronic GvHD incidence and grade, and overall survival rate. Regarding the primary outcome, we hypothesise that, compared to the usual-care/control group, patients receiving the SMILe-ICM will have a lower re-hospitalisation rate. As for the secondary outcome set, compared to the control group, we expect to see lower total healthcare utilization costs, shorter lengths of re-hospitalizations, lower medication non-adherence (implementation phase of adherence [67]), less treatment burden, better HRQL, higher quality-adjusted life years (QALY), and equal medical outcomes (acute and chronic GvHD incidence, overall survival).
**1b.** to extend objective **1a** by testing for a potential wane-out of the SMILe-ICM intervention effect in view of primary and secondary outcomes during the three-month post-intervention follow-up.
**Aim 2** is to evaluate the SMILe–ICM’s bundle of implementation strategies and assess acceptability, appropriateness, feasibility, and fidelity (implementation outcomes) as well to evaluate the implementation pathway (as viewed by patients and health care professionals).

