### Context and targeted sites

In Switzerland, nearly 250 alloSCTs are performed annually. Roughly 110 of these take place at the USB, which is the largest alloSCT program in Switzerland [70]. The USB has a designated alloSCT unit and outpatient clinic, as well as a specialised alloSCT medical and nursing staff. Patients are hospitalised about 10 days before their transplantation. After it, depending on their state of health, they remain in hospital an average of 25 days. As noted, post-transplant monitoring and care follow an outpatient follow-up schedule. Depending on the patient’s state of health, post-transplant care then can be transferred to closely-collaborating external centres. Patients from the Switzerland’s Italian-speaking region (Ticino) receive their follow-up care solely at the haematology departments closest to their homes.

One issue revealed by the current study’s contextual analysis (Phase A) is that, once patients are discharged, they receive a low mean level of chronic illness management including limited self-management support. The clinician group most qualified to remedy this shortfall would be the APNs. However, while they are involved in immediate post-transplant care and discharge planning, longer-term post-transplant management is not yet organised as a multidisciplinary topic.

An academic service partnership between the USB and the University of Basel’s Institute of Nursing Science (INS) provides the infrastructure that supports the SMILe project. Two of the SMILe investigators (SV, JR) work in joint INS/USB appointments.

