#### Analysis

Statistical analyses will be conducted at the University of Basel’s Institute of Nursing Science using the R software package [96]. Data cleaning will include systematic screening for out-of-range values and data inconsistencies. Multiple imputations will be considered for missing data. Descriptive statistics will be applied as appropriate for all variables.
***Aim 1a:*** To determine whether hospitalisation rates (primary outcome) are reduced via the SMILe-ICM’s implementation, we will analyse any differences between IG and UCG rates by applying generalised linear mixed models (GLMM) [97]. The relevant variables (i.e., time, study group, and group x time interaction) will be entered into the models. Our targeted test statistic is the rate ratio by unconditional maximum likelihood estimation (Wald) as described by Rothman et al. [98] and implemented in epitools [99]. We will conduct intention-to-treat and per-protocol analysis. Two-sided significance will be set at 0.05. To analyze the target secondary outcomes over the course of time, descriptive analyses will be carried out and GLMM will be used to determine differences between the IG and UCG. Cost data will be collected and analysed quarterly. Overall survival will be analysed using the Kaplan-Meier method and the log-rank test. To analyse QALY, we will use the EQ-5D-5L**©** value set for Germany. The electronically compiled dosing history will be analysed using by applying GLMM, which account for dependence among observations from a single patient over time. The resulting estimates will be expressed as odds ratios (ORs) [100].
***Aim 1b:*** To test a potential wane-out effect of the SMILe-ICM’s intervention effect over 3 months’ post-intervention follow-up, differences between the IG and the UCG will be determined by applying GLMM. This approach allows calculation of the main group and time effects, and of group-by-time interaction effects. Two-sided significance will be set at 0.05.

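### Length of re-hospitalisation is a raw total of days with no allowance for time alive and at risk, and its counting window can be read two ways

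*Protocol article*

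**What the plan says.** In the protocol article, Table 3 (Secondary Outcomes, Length re-hospitalizations) opens its definition with "The total length of inpatient re-hospitalizations in the first year after alloSCT" and goes on to say that this "is the total number of hospitalized days (planned and unplanned) after initial post-alloSCT discharge until end of study". It is a sum of days. It has no denominator and no rule for patients who die or are never discharged.

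Study aims (Aim 1a) lists "shorter lengths of re-hospitalizations" among the expected advantages of the intervention. The Background (The SMILe project) states that "mortality and re-hospitalisation rates remain substantial, especially in the first year post-alloSCT". Context and targeted sites says that after transplantation, depending on state of health, "they remain in hospital an average of 25 days".

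For secondary outcomes in general, the Analysis section says that "GLMM will be used to determine differences between the IG and UCG". It mentions no exposure term for this outcome. Overall survival is analysed separately by Kaplan-Meier and log-rank. Table 2, by contrast, expresses the primary outcome per patient year.

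**The concern.** Re-hospital days can accrue only while a patient is alive and has already been discharged once. For a given hospital course, cutting the course short by death can only lower the total or leave it unchanged. A long index stay also shortens the counting window, and its days are not counted. Death and first discharge both happen after randomisation, so allocation does not guarantee that time at risk is balanced between arms.

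A difference in total days could therefore reflect different hospital use, different survival, different index stays, or a mixture, and the total alone cannot separate them. An imbalance in deaths could produce an apparent saving in days or mask a real one.

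The window is a separate problem. If counting runs through the three months after the intervention ends, the Aim 1a result absorbs the period that Aim 1b is meant to examine on its own.

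**Working it through.** The protocol gives no expected value for this outcome, so there is no figure to reproduce. The check asks how far the definition alone can move the comparison when hospital use per day alive is identical in both arms.

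**Inputs from the protocol:** first discharge about day 25; year-one visit at day 365 and last visit at day 455 (Table 2); 1.56 hospitalisations per patient year and shape parameter 4, read here as negative binomial (Sample size determination); 40 patients per arm.

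**Assumed, because the protocol gives no figures:** one-year mortality, timing of deaths, 10 or 20 days per admission, and 0, 10 or 20 extra days in a terminal admission.

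**1. Days at risk for one patient.** A survivor to day 365 has 365 − 25 = 340 days.

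| Course | Days at risk | Share of 340 |
|---|---|---|
| Death on day 60 | 35 | 10% |
| Death on day 100 | 75 | 22% |
| Death on day 180 | 155 | 46% |
| Survivor, first discharge day 60 | 305 | 90% |
| Survivor, first discharge day 90 | 275 | 81% |

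**2. Ratio of arm totals from mortality alone.** Mean days at risk = (1 − m) × 340 + m × (death day − 25).
- Deaths at day 150, 25% mortality: 0.75 × 340 + 0.25 × 125 = 286.3. With 15%: 0.85 × 340 + 0.15 × 125 = 307.8. Ratio 0.93.
- Deaths at day 75: 267.5 / 296.5 = 0.90.
- Equal mortality and timing: ratio 1.00.

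**3. Simulation.** Each scenario had 400,000 patients, with gamma-Poisson admissions at 1.56 per year (shape 4), exponential time to death and the same admission rate in both arms.

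| Scenario | Ratio of raw totals | Ratio per time alive |
|---|---|---|
| 30% vs 20% mortality, no terminal stay, to day 365 | 0.94 | 1.00 |
| 40% vs 20%, no terminal stay, to day 365 | 0.87 | 1.00 |
| 30% vs 20%, no terminal stay, to day 455 | 0.92 | 1.00 |
| 40% vs 20%, no terminal stay, to day 455 | 0.84 | 1.00 |
| 30% vs 20%, 10 to 20 terminal days, either window | 0.95 to 1.05 | 1.04 to 1.13 |

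Time alive as exposure removes the artefact when there is no extra terminal stay. With terminal stays the raw ratio can fall on either side of 1, and the per-time ratio is itself pushed above 1.

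**4. How likely is a chance imbalance?** With 40 per arm and 20% mortality in both, a gap of at least 10 points (4 deaths) has an exact binomial probability of about 33% in either direction, and about 16% with the excess in the intervention arm. At 10% to 30% mortality the either-direction figure runs from 19% to 39%.

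**5. Size against noise.** Mean admissions over 340 days: 1.56 × 340/365 = 1.45. With constant stay length, the standard error of the log ratio is √[2 × (1/1.45 + 1/4)/40] ≈ 0.22. A ratio of 0.93 is a log shift of 0.07, about one-third of a standard error. A ratio of 0.90 is a shift of about 0.10, roughly half. Variable stay lengths would make these fractions smaller.

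**6. Window.** (455 − 25)/(365 − 25) = 430/340 = 1.26, so a survivor has 26% more time to accrue days under the longer reading.

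**The case against.** The strongest reply is that a condensed article need not spell out an offset or a rule for death. A GLMM can take an exposure term, and Table 2 schedules length of stay at each visit, so an interval analysis would simply stop at death. Table 3 may also be shorthand: its entry for the primary outcome omits patient-time as well, although Table 2 gives a rate per patient year. This carries some weight, because an analysis plan not shown could repair the comparison. But the point rests on what the article does state, which is a cumulative total with fewer days hypothesised as better.

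A reader might infer that early death is simply rewarded as a benefit. The documents do not support that as a net result. It holds if hospital use per day alive is constant, but the Background describes life-threatening complications in the first months, and long final admissions could cancel or reverse the effect. A patient who dies before first discharge does not clearly score well either; the value is undefined. The protocol also expects equal survival, and deaths will be visible in the separate survival analysis.

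A reader might also call the window a flat contradiction. Randomization process describes the study's duration as running to one year post-transplant with three months' follow-up, which allows a one-year reading. Sample size determination gives a 15-month observation period, which supports the longer one. It is an ambiguity.

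Finally, replacing the outcome with days alive and out of hospital from transplant would change the estimand by adding the index stay and mortality. That is a trade-off, and the protocol is not wrong to want re-hospital days.

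**Conclusion.** The point holds in a limited form. As defined, the outcome mixes hospital use with time alive and at risk, and the comparison between arms is distorted if deaths or first-discharge timing differ. The lowering of about 7 to 10% in the higher-mortality arm rests on an assumed 25% versus 15% mortality, deaths at day 150 or day 75 on average, and equal use per day alive. It is one-third to one-half of a standard error at most, it can vanish or reverse with 10 to 20 terminal days, and it is zero when mortality and discharge timing are equal. The window ambiguity needs no mortality assumption and is worth 26% of a survivor's time at risk. This is one secondary outcome and the primary conclusion is untouched, but the repair is cheap enough that it should be made.

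**What to change.** - Keep the outcome, but analyse re-hospital days with time alive from first discharge as the exposure, either as an offset in the GLMM or as days per patient-year alive.
- State that patients who die before first discharge have no time at risk, and report deaths by arm beside the result.
- Add days alive and out of hospital to day 365 as a sensitivity analysis, because a per-time rate is still distorted by terminal stays.
- Reword the definition so that the Aim 1a window ends at day 365, and analyse days 366 to 455 separately under Aim 1b.

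The cost is a change of wording and one extra analysis of a secondary outcome. Hospital days and date of death are already collected (Tables 2 and 3), so no new data are needed. The sensitivity measure combines mortality with hospital use, so it should be read beside the main result and not in place of it.

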#### Effectiveness outcomes

The primary effectiveness outcome will be the re-hospitalisation rate. Table 3 summarises primary and secondary effectiveness outcomes and their measurement. Specifically for the Swiss setting [63], medication adherence is assessed in addition to a self-report scale (BAASIS©) also using the MEMS® Button [86] electronic monitoring (EM) device. The latter device being integrated in the study based on a qualitative exploration on patient preferences and patient’s evaluation of its usability in daily life [63].

